## Abstract

**Introduction:**

Current evidence on vascular access strategies for haemodialysis patients is based on observational studies that are at high risk of selection bias. For elderly patients, autologous arteriovenous fistulas that are typically created in usual care may not be the best option because a significant proportion of fistulas either fail to mature or remain unused. In addition, long-term complications associated with arteriovenous grafts and central venous catheters may be less relevant when considering the limited life expectancy of these patients. Therefore, we designed the Optimising Access Surgery in Senior Haemodialysis Patients (OASIS) trial to determine the best strategy for vascular access creation in elderly haemodialysis patients.

**Methods and analysis:**

OASIS is a multicentre randomised controlled trial with an equal participant allocation in three treatment arms. Patients aged 70 years or older who are expected to initiate haemodialysis treatment in the next 6 months or who have started haemodialysis urgently with a catheter will be enrolled. To detect and exclude patients with an unusually long life expectancy, we will use a previously published mortality prediction model after external validation. Participants allocated to the usual care arm will be treated according to current guidelines on vascular access creation and will undergo fistula creation. Participants allocated to one of the two intervention arms will undergo graft placement or catheter insertion. The primary outcome is the number of access-related interventions required for each patient-year of haemodialysis treatment. We will enrol 195 patients to have sufficient statistical power to detect an absolute decrease of 0.80 interventions per year.

**Ethics and dissemination:**

Because of clinical equipoise, we believe it is justified to randomly allocate elderly patients to the different vascular access strategies. The study was approved by an accredited medical ethics review committee. The results will be disseminated through peer-reviewed publications and will be implemented in clinical practice guidelines.

**Trial registration number:**

NL7933.

**Protocol version and date:**

V.5, 25 February 2021.

Strengths and limitations of this studyThis is the first prospective trial randomly allocating elderly haemodialysis patients to the three commonly used vascular access strategies.By enrolling patients on referral for vascular access creation, the trial will reflect everyday practice and study patients with predialysis vascular access creation as well as patients who have started dialysis urgently with a temporary catheter.The primary outcome, that is, the number of access-related interventions required for each year of haemodialysis treatment, corresponds to the recently proposed core outcome measure for clinical trials in vascular access.A previously published mortality prediction score was validated to determine a cut-off point for exclusion of elderly patients with an unusually long life expectancy for whom a fistula is still considered to be the best vascular access.

## Introduction

The haemodialysis population has been growing older and older over the past decades, and the median age of patients starting haemodialysis treatment today is 66 years.^1^ These patients need a reliable vascular access that may be provided by autologous arteriovenous fistulas, prosthetic arteriovenous grafts and central venous catheters. Autologous fistulas are created by surgically anastomosing a superficial vein to an artery in the upper extremity. After creation of the fistula, vascular remodelling will increase venous outflow diameter and blood flow, a process referred to as maturation. Functional fistulas are generally associated with the best long-term outcomes. However, a substantial proportion of fistulas fail to mature and never become functional.^2^ Arteriovenous grafts are placed by interposing a prosthetic vascular graft between an artery and a vein in a subcutaneous track in the upper extremity. Grafts do not need time to mature but are associated with a higher incidence of infection, stenosis and thrombosis than functional fistulas.^3^ Central venous catheters are inserted in the internal jugular vein with a minimally invasive procedure and can be used immediately after placement. However, catheters have been associated with increased bloodstream infections and mortality compared with other vascular access types.^3 4^ Studies comparing these different vascular access strategies typically focus on functional outcomes, and little is known about differences in patient-reported outcome measures (PROMs) and healthcare costs.

Clinical practice guidelines on vascular access have long recommended the creation of autologous arteriovenous fistulas regardless of patient characteristics.^5^ However, this recommendation is based solely on observational studies that are at high risk of bias. Patients who have a fistula created prior to starting dialysis generally have more favourable baseline characteristics and a lower mortality risk than other patients.^6^ These favourable patient characteristics may account for two-thirds of the survival benefit seen in patients using arteriovenous fistulas for haemodialysis treatment instead of central venous catheters.^7^ Further selection bias will occur as patients are analysed according to vascular access use. This tends to favour autologous fistulas since the poor subset of patients with fistulas that have failed to mature will go on to use a different type of vascular access. When primary fistula failures are taken into account, the cumulative patency of fistulas and grafts become comparable.^8^ Finally, observational studies based on dialysis registries do not include patients with arteriovenous fistulas created before dialysis initiation that were never used because of patient death or stable renal function.

Uncertainty regarding the best type of vascular access is particularly important for elderly patients starting haemodialysis treatment. In these patients, autologous arteriovenous fistulas have a 40% increased risk of non-maturation and early failure.^2^ Moreover, 30% of fistulas created before initiation of dialysis treatment in elderly patients will never be used because of patient death, stabilisation of renal function or choice for conservative treatment as the patient’s condition worsens over time.^9^ Furthermore, the increase in long-term complications associated with arteriovenous grafts may be less relevant for elderly patients with a limited life expectancy. Finally, elderly patients have a 30% lower risk of complications of central venous catheters, including bloodstream infections.^4 10^ Considering this clinical equipoise, the need for better evidence on vascular access strategies in elderly haemodialysis patients is broadly recognised. Indeed, international experts on vascular access surgery as well as patient representatives have called for a randomised trial comparing vascular access strategies in elderly haemodialysis patients.^5 11^

We performed a comprehensive search in international trial registers for ongoing and planned randomised trials on vascular access creation in elderly haemodialysis patients. Four ongoing trials were identified that allocate participants to arteriovenous fistula or graft surgery. One trial has a single-centre design and plans to enrol 270 haemodialysis patients aged 70 years or older. The participants are followed up for 2 years after vascular access creation for the primary outcomes, which are vascular access use as well as patency.^12^ The remaining three trials are pilot studies evaluating the feasibility of the trial design. These pilot studies allocate patients aged 65 years or older, either at the time of referral for vascular access, at dialysis initiation or after dialysis initiation with a catheter.^13–15^ We also identified two trials allocating participants to fistula creation or catheter insertion. The ACCESS HD feasibility study allocates patients aged 55 years or older who have already commenced haemodialysis treatment with a catheter to either fistula creation or continued catheter use.^11^ The AUSTrian Randomized Interventional Study on Dialysis Accesses (AUSTRIA) aims to allocate 220 participants aged 60 years or older to one of the two treatment arms, with access-related complications being the primary outcome measure.^16^ Although these ongoing studies will surely provide valuable information, none of the trials cover the full spectrum of vascular access strategies in elderly haemodialysis patients.

The aim of the Optimising Access Surgery in Senior Haemodialysis Patients (OASIS) trial is to determine the best vascular access strategy for elderly haemodialysis patients. We hypothesise that arteriovenous grafts and central venous catheters are superior to autologous arteriovenous fistula for elderly patients starting haemodialysis treatment and result in reduced access-related intervention rates, greater patient satisfaction and lower healthcare costs.

## Methods and analysis

### Study design

OASIS is a parallel group, multicentre, randomised controlled trial with a superiority framework and a 1:1:1 individual participant treatment allocation ratio over three study arms. Given the nature of the interventions, blinding healthcare providers, participants or outcome assessors for treatment assignment are not possible. However, data analysis will be performed without knowledge of treatment assignment by coding the treatment arms and unlocking the code only after statistical analysis is completed. Some 17 hospitals, together treating approximately 50% of all haemodialysis patients in the Netherlands, are expected to participate.

### Study population

On referral for permanent vascular access creation, all patients will have a preoperative duplex ultrasound assessment of the blood vessels of the upper extremities. This preoperative workup may be supplemented by central venous phlebography and arterial imaging as considered appropriate by the local vascular access team. All potential participants will receive oral and written information about the trial by the local investigators and are registered in a screening log.

#### Inclusion criteria

Age 70 years or older.End-stage renal disease with unlikely recovery of kidney function according to the attending nephrologist.Haemodialysis is the intended long-term modality of treatment for end-stage renal disease.Fit for any of the proposed vascular access interventions as determined by the local multidisciplinary vascular access team.(1) Expected to start haemodialysis treatment within 6 months at the time of treatment assignment, or (2) treated with haemodialysis for 6 months or less at the time of treatment assignment using a tunnelled or non-tunnelled central venous catheter for vascular access.Planning to remain in one of the participating dialysis centres for at least 1 year.Suitable vascular anatomy for all types of vascular access based on duplex ultrasound of the arms, defined as^5^
At least one suitable configuration for an arteriovenous fistula using minimal arterial and venous diameters of 2 mm for radiocephalic fistulas and 3 mm for brachiocephalic and brachiobasilic fistulas;At least one suitable configuration for an arteriovenous graft using minimal arterial and venous diameters of 3 and 4 mm, respectivelyAt least one open internal jugular vein for a central venous catheter.

#### Exclusion criteria

Patent arteriovenous fistula or graft already in place.Prior unsuccessful arteriovenous fistula or graft vascular access surgery.Kidney transplantation scheduled within 6 months.Metastatic malignancies or other condition associated with a life expectancy of <6 months, in the opinion of the attending nephrologist.Unable to provide informed consent.Dusseux risk score of ≤4, indicating an unusually long life expectancy.^17^

Patients will be enrolled by local investigators if they meet the eligibility criteria and provide informed consent. Local investigators will be informed of treatment assignment through a web-based service, after which vascular access creation is planned according to usual clinical care for the allocated vascular access type at the study site (figure 1). The treatment allocation sequence is generated by an independent data management centre using a computer-based random number-producing algorithm. Block randomisation is implemented with randomly varying block sizes of 3 and 6, and randomisation will be stratified by treatment centre. Follow-up starts immediately after treatment allocation.

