#### Central venous catheters

Patients who are allocated to the catheter strategy will have a dialysis catheter inserted, unless they have already started haemodialysis with a tunnelled catheter. We recommend placing a tunnelled catheter just before the start of haemodialysis treatment. We advise following published guidelines for the prevention and treatment of catheter infections.^23^ In case of catheter dysfunction despite local thrombolytic agents, the catheter can be exchanged.^24^

For the arteriovenous fistula and graft group, surveillance and pre-emptive intervention for stenosis will take place according to usual practice at the study sites. In case of failure, both endovascular and surgical interventions can be undertaken to restore patency. If the assigned vascular access strategy proves not to be feasible, patients will cross over to one of the other treatment groups after discussion of the case with the principal investigator. Use of a temporary central venous catheter is not considered as a treatment group crossover.

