### Data analysis plan

The access-related intervention rates will be analysed using a general linear model with Poisson distribution and identity link, and with time as off-set variable. Both intervention (ie, the prosthetic arteriovenous graft and central venous catheter) groups will be compared with the usual care (autologous arteriovenous fistula) group. Non-adherence to the allocated treatment group is expected as patients cross over to another surgical strategy for vascular access when the randomised strategy is no longer feasible. The primary analysis will be on the intention-to-treat population. Exploratory on-treatment analyses will be performed as well. A subgroup analysis will be performed for patients who had already started haemodialysis using a catheter before inclusion.

Formal statistical comparisons will be made for the following secondary study outcomes:

SF-12/DSI and SF-VAQ summary scores using generalised estimating equations.The number of access-related serious adverse events per person-year using general linear models with Poisson distribution and mortality using Cox regression.The number of days admitted to the hospital or visiting outpatient clinics for any reason per person-year using Student’s t-tests.

Primary outcome data are not expected to be missing, as interventions on vascular access will be reported in the patients’ medical files. We expect little to no loss to follow-up since study participants will be observed three times per week in the dialysis unit and the trial requires no additional study visits. PROMs will be analysed using generalised estimating equations that allow for missing data. Other missing data will be handled by using 10 imputation cycles with regression methods, performing standard analyses for each imputation cycle and considering the variability across the imputation cycles in the final analysis.

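### The primary model as described names neither the stratification factor (centre) nor dialysis status at randomisation; once the standard error allows for overdispersion, leaving them out gives up precision

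*Protocol article*

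**What the plan says.** All references are to the protocol article.

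- **Randomisation** (end of Exclusion criteria): "randomisation will be stratified by treatment centre". In addition, "Block randomisation is implemented with randomly varying block sizes of 3 and 6". Centre is the only stratification factor named.
- **Design** (Study design): "Some 17 hospitals, together treating approximately 50% of all haemodialysis patients in the Netherlands, are expected to participate", with a "1:1:1 individual participant treatment allocation ratio over three study arms".
- **Site practice** (Interventions): the trial does not interfere with sites' surgical protocols. For fistulas and grafts, "surveillance and pre-emptive intervention for stenosis will take place according to usual practice at the study sites".
- **Dialysis status** (Inclusion criteria): one route of entry is "Expected to start haemodialysis treatment within 6 months at the time of treatment assignment". The other is up to 6 months of haemodialysis through a catheter.
- **Primary model** (Data analysis plan): a "general linear model with Poisson distribution and identity link, and with time as off-set variable". The two intervention "groups will be compared with the usual care (autologous arteriovenous fistula) group". No covariate is named and none is ruled out. Dialysis status appears only as a subgroup analysis.
- **Sample size calculation**: an unadjusted two-group Poisson rate-difference test, so the stated power claims no gain from covariates.

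**The concern.** Centre is what the trial randomises by, and it plausibly drives the outcome: the primary endpoint counts every percutaneous, surgical and catheter intervention, and sites decide their own surgical and surveillance practice. Stratified randomisation makes the treatment estimate more precise when centres differ. An analysis that ignores centre but uses an empirically valid standard error does not credit that precision and becomes conservative.

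Dialysis status is a separate case. It is not a stratification factor, so the argument for it is prognostic. The primary outcome includes interventions before dialysis starts but divides by haemodialysis years, so status at entry can affect both numerator and denominator. Chance imbalance between arms is left uncorrected.

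At stake is precision in a trial planned at 80% power, and a stated link function that makes the obvious remedy hard to apply.

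**Working it through.** **1. The plan's own figure.** Inputs from Sample size calculation: rates 2.48 and 2.48 − 0.80 = 1.68 per year, two-sided alpha 0.025 (z = 2.241), 80% power, 1 year each.

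- Without continuity correction: n = (2.241 + 0.842)² × (2.48 + 1.68) / 0.80² = 61.8, so 62 per arm. Power at 65 is 82.1%.
- With continuity correction, power = Φ[(0.80 − 1/n)/√(4.16/n) − 2.241]: 79.8% at n = 64 and 80.5% at n = 65. The stated 65 per arm is reproduced.

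**2. Mechanism, by hand (log scale, centre only).**

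- Poisson floor for the SE: √[1/(65 × 2.48) + 1/(65 × 1.68)] = 0.124. Effect: ln(2.48/1.68) = 0.389, which is 3.142 standard errors.
- Plain Poisson SE: power = Φ(3.142 − 2.241) = 82%. A Poisson model estimates no residual variance, so omitted centre variation does not widen this SE.
- Dispersion-scaled SE without centre, assumed centre CV 0.3: mean count (2.48 + 1.68)/2 = 2.08, dispersion about 1 + 2.08 × 0.3² = 1.187, so the SE is inflated by √1.187 = 1.09. Stratification keeps the true SE near 0.124, so power = Φ(3.142 − 1.09 × 2.241) = Φ(0.70) = 76%.

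**3. Simulation.** 17 centres, blocks of 3 and 6, 65 per arm, 1 year each, log-link Poisson, half the patients assumed already on dialysis. Arrows run from unadjusted to adjusted for centre and dialysis status. 2,000 trials per cell, no patient frailty:

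| Centre CV / status rate ratio (assumed) | Power, Poisson SE | Power, scaled SE | Type I error, Poisson SE (nominal 2.5%) |
|---|---|---|---|
| 0 / 1 | 82.4 → 81.6% | 82.4 → 81.9% | 2.3 → 2.2% |
| 0.2 / 1.25 | 81.6 → 80.8% | 78.8 → 80.7% | 2.4 → 2.0% |
| 0.3 / 1.5 | 82.6 → 82.4% | 75.1 → 82.3% | 3.3 → 2.2% |
| 0.4 / 2.0 | 77.4 → 79.5% | 59.6 → 79.5% | 5.1 → 2.8% |

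On the rate-difference scale with the plain Poisson variance, stratifying the analysis by centre also changes little: 82.3% against 82.1% at CV 0.2, and 82.6% against 82.4% at CV 0.4.

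**4. The range used in the conclusion: centre CV 0.3, scaled SE.** The second column is a repeat with 3,000 trials per cell.

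| Setting | Power | Repeat |
|---|---|---|
| Centre only | 77 → 81% | 77 → 82% |
| Plus status rate ratio 1.5 | 75 → 83% | 73 → 81% |
| Plus frailty variance 0.25 | 55 → 66% | 52 → 61% |

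The gains are 4, 8 and 11 points, and in the repeat 5, 8 and 9 points: roughly 4 to 10. In the repeat, type I error was 1.5 to 2.0% unadjusted and 2.7 to 3.5% adjusted. The unadjusted test is therefore conservative, and the adjusted SE runs slightly low.

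**5. Identity link.** 195/17 is about 11 patients per centre, or about 4 per arm. Adding centre indicators and dialysis status to an identity-link Poisson fit (700 trials per cell, multiplicative data, standard iteratively reweighted least squares) gave non-convergence or non-positive fitted means in 19%, 37% and 70% of trials for the last three rows of the first table under the planned effect, and in 6%, 14% and 38% under the null.

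**6. Dialysis-status imbalance.** With an assumed 50:50 mix, the SD of the between-arm difference is √(2 × 0.25/65) = 8.8 percentage points.

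**The case against.** **The omission is read from silence.** A reader might infer that the primary model contains treatment arm and time only. The article does not say so. It is a condensed account, and a covariate list may stand in the full protocol or the SAP, neither of which is shown. This objection stands as to what the final analysis will contain. It does not dispose of the point, because the article does fix the distribution, link, offset and comparisons, and the fixed identity link is the element that takes centre and status terms badly.

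**Power is not lost under the analysis as written.** A reader might infer that ignoring centre costs power outright. That carries over reasoning from the normal linear model. With a model-based Poisson SE the change is about 0 to 2 points, and the larger consequence is mild inflation of type I error, up to 5.1% in the most heterogeneous case. The precision argument holds only once the SE is made valid for overdispersion, which the article does not mention. Nor could adjustment lift power well above the planned level: at 65 per arm and 1 year the Poisson floor caps it at about 82%.

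**The heterogeneity is assumed.** No between-centre variation is given, and sites are expected to follow guidelines. Surveillance concerns the fistula and graft arms only, so part of its variation is specific to arm and a main effect of centre will not remove it. Both stand.

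**Dialysis status is ordinary chance imbalance.** It causes no bias on average, and a subgroup analysis is planned. This is correct; the case for adjusting is precision alone.

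**Adjustment does not cure overdispersion.** This also stands. With the plain Poisson SE, type I error stays near 8 to 10% at an assumed frailty variance of 0.25, and at about 13 to 15% at 0.5, even after adjustment.

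**Conclusion.** The point holds in conditional form. The trial randomises by centre and lets site practice generate outcome events, yet the described primary model names neither centre nor dialysis status and uses a link that accommodates them poorly. Under a plain Poisson SE the omission is nearly neutral for power. Under an SE valid for overdispersion, the unadjusted analysis gives up roughly 4 to 10 points of power at 65 per arm and 1 year, part of which may reflect a slightly low adjusted SE.

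That range rests on an assumed centre CV of 0.3, a status rate ratio of 1 to 1.5, a frailty variance of 0 to 0.25 and half the patients already dialysing. Smaller heterogeneity gives less (about 2 points at CV 0.2 and rate ratio 1.25), larger gives more. The documents support neither an unconditional loss of power nor the claim that covariates are excluded. The change is worth making because it is cheap and both variables are known at randomisation; it does not expose an invalid comparison.

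**What to change.** State in the analysis plan, before the treatment code is unlocked, that the primary model includes:

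- centre, as a random intercept, or as fixed effects with small centres pooled by a prespecified rule;
- dialysis status at randomisation (not yet dialysing, or already dialysing by catheter).

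Fit the model on a scale that accepts these terms, such as a log link. Then obtain the adjusted difference in interventions per year by marginal standardisation, so that the planned rate-difference estimand is kept. Use a dispersion-scaled or small-sample-corrected robust standard error. The two parts belong together, since covariates alone do not deal with patient-level overdispersion and a valid standard error alone leaves the unadjusted test conservative. If the full protocol or SAP already does this, confirm it and reconcile the identity link with it.

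Cost: analysis-plan wording, a pooling rule for small centres and slightly more analysis work. No new data and no change to randomisation.
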